### Assessment of baseline variables

Baseline variables of all included patients will be tabulated. Discrete variables will be reported as frequencies and percentages, and continuous variables will be reported as either means with SDs or medians with interquartile ranges as appropriate.

### Analysis of outcomes

Study outcomes will be analyzed using a Wilcoxon rank-sum test. A non-parametric test was chosen since such tests are more robust to outliers, which can have undue influence on the results of a parametric test for a small number of patients. In the event of no difference between the groups with regard to secondary outcomes and a difference in the primary outcome (glucose absorption lower in the optimized group), we will interpret such results as supporting our hypothesis but that confirmatory studies are needed using a higher number of patients since the low *N* in the current study may not be adequately powered to detect differences in the secondary outcomes. In this situation, a Monte Carlo-based sensitivity analysis will be performed to quantify the minimal difference needed to yield a significant difference in the secondary outcomes.

In the case of both a significant difference between the groups with regard to secondary outcomes and in the primary outcome (with glucose absorption lower in the optimized group), we will interpret these results as supportive of our hypothesis if the difference in secondary outcomes implies an improvement. Indeed, due to stirring effects, the higher DFR associated with the optimized regimes may result in improved NaR, urea, and creatinine clearance and UF [2]. In any other case, the differences will be compared to the differences expected theoretically according to the extended 3-pore model [2].

Should the primary outcome be negative or show a higher glucose absorption for the optimized regimen, then, all other outcomes are regarded as exploratory, with the exception of number of complications, and no emphasis will be placed on any differences between the treatment groups.

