**Methods:**

This study is a randomized single-center, open-label, prospective study. Prevalent PD patients between 18 and 75 years old without known catheter problems or recent peritonitis are eligible for inclusion. Patients are allocated to a first treatment session of either standard APD (6 × 2 L 1.36% over 9 h) or optimized APD (7 × 2 L 2.27% + 5 × 2 L 0.1% over 8 h). A second treatment session using the other treatment will be performed in a crossover fashion. Samples of the dialysis fluid will be taken before and after the treatment, and the volume of the dialysate before and after the treatment will be carefully assessed. The primary endpoint is difference in glucose absorption between the optimized and standard treatment. Secondary endpoints are ultrafiltration, sodium removal, Kt/V urea, and Kt/V Creatinine. The study will be closed when a total of 20 patients have successfully completed the interventions or terminated according to interim analysis. A Monte Carlo power analysis shows that the study has 80% power to detect a difference of 10 g (in line with that of theoretical results) in glucose absorption between the two treatments in 10 patients.

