### Sample size and power analysis

Published relative standard error values for glucose absorption comprise values ranging from 10 to 30% with a mean of 18% [3]. The worst performance for the optimized regime is a reduction in glucose absorption of about 10 g. Thus, a Monte Carlo-based power analysis was performed by the generation of 10,000 random samples *S* and *O* of size *N* from two normal sampling distributions having *μ* = 44 g; *σ* = 7.74 and *μ* = 34 g; *σ* = 5.94. The theoretically expected difference will differ depending on transport type and is higher with a faster peritoneal membrane. A Wilcoxon rank-sum test was performed to assess the statistical difference between the samples *S* and *O*. The statistical power was calculated as the number of significant (*P* < 0.05) results, for example, 8687/10,000 implies a statistical power of ~ 87%. The procedure was repeated by step-wise increasing *N* until a statistical power of > 80% was attained, which occurred at *N* = 10. For *N* = 20, the statistical power was found to be > 98%.

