### Statistical analysis plan

The study will continue until a total of 20 patients have been included. This number is higher than that estimated in the power analysis. However, only patients who successfully completed both treatment regimens will be included in the analysis. Due to the complicated technical nature of the experimental setup, there may be a significant amount of unusable results, and the relative over-recruitment is aimed at compensating for a high post-allocation exclusion rate. The investigating team will perform the statistical analyses. In general, (1) analysis will be performed on a per-protocol basis, (2) all hypothesis tests will be paired and two-sided, with a maximal type I error risk of 0.05 ,and (3) imputation will not be used to correct for missing data in the analysis.

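### The analysis section names an independent-samples rank-sum test for a crossover trial whose own rule is that every test is paired; the result is a conservative test, and the interim rule must be aligned with any correction

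*Protocol article*

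**What the plan says.** - **Design** (abstract, Methods): "A second treatment session using the other treatment will be performed in a crossover fashion". Each patient therefore receives both regimens.
- **Statistical analysis plan section**: "all hypothesis tests will be paired and two-sided, with a maximal type I error risk of 0.05". The same section says that "only patients who successfully completed both treatment regimens will be included in the analysis".
- **Analysis of outcomes**: "Study outcomes will be analyzed using a Wilcoxon rank-sum test". This covers the primary outcome and all secondary outcomes.
- **Sample size and power analysis**: the simulation draws from "two normal sampling distributions having *μ* = 44 g; *σ* = 7.74 and *μ* = 34 g; *σ* = 5.94", with no correlation between the two draws, and "A Wilcoxon rank-sum test was performed to assess the statistical difference between the samples". The section reports more than 80% power at N = 10 and more than 98% at N = 20.
- **Interim analysis**: after 10 completers the trial may stop for efficacy at P ≤ 0.001 on the primary endpoint. Futility is judged with a two-sided Student's t test, without saying whether it is paired.

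**The concern.** The two instructions cannot both be followed. Applied to the two columns of treatment values, the rank-sum test treats 20 patients measured twice as 40 unrelated observations and gives up the within-patient comparison that the crossover provides. The paired counterpart is the Wilcoxon signed-rank test.

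This is not safely a slip of one word. The power simulation applies the same rank-sum test to two separately generated samples, and the analysis section speaks of groups. An analyst could follow either statement and claim to be on plan.

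Three things are at stake: the error rate and power of the primary test; the sensitivity of the tests of ultrafiltration, sodium removal and Kt/V, for which the hypothesis is no difference and a null result is counted as supportive; and whether the interim efficacy rule can operate, since that depends on which test is meant.

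**Working it through.** **Inputs.** From the sample size section: means 44 g and 34 g, SDs 7.74 and 5.94, two-sided 0.05. From the other sections: 20 patients planned, interim at 10 completers, boundary P ≤ 0.001. The within-patient correlation ρ is not in the document, so every result for ρ > 0 is an assumption shown over a range.

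**Step 1: reproduce the stated power.** Independent normal samples, N values per regimen, exact two-sided rank-sum test, 20,000 replicates:

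| N | Power |
|---|---|
| 9 | 76.8% |
| 10 | 82.3% |
| 20 | 99.0% |

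This matches the stated N = 10 and more than 98% at N = 20. N must mean values per regimen, that is, crossover patients; 5 values per arm gives only 41%.

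**Step 2: what pairing changes.** The variance of a within-patient difference is σ_S² + σ_O² − 2ρσ_Sσ_O = 59.91 + 35.28 − 91.95ρ.
- ρ = 0: 95.19, SD 9.76 g
- ρ = 0.3: 67.61, SD 8.22 g
- ρ = 0.5: 49.22, SD 7.02 g
- ρ = 0.7: 30.83, SD 5.55 g

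The rank-sum test is calibrated for the ρ = 0 line whatever ρ is. For ρ > 0 it overstates the noise and rejects too seldom.

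**Step 3: true two-sided type I error of the rank-sum test on pairs** (nominal 5%, bivariate normal):

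| ρ | N = 10 | N = 20 |
|---|---|---|
| 0 | 4.5% | 4.8% |
| 0.3 | 2.1% | about 2% |
| 0.5 | 1.1% | about 1% |
| 0.7 | 0.4% | 0.1–0.2% |

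The signed-rank test stays near 5% throughout.

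**Step 4: power for the planned 10 g difference** (rank-sum / signed-rank):

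| ρ | N = 10 | N = 20 |
|---|---|---|
| 0 | 82.7% / 80.6% | 99.1% / 98.9% |
| 0.3 | 85.8% / 91.4% | 99.7% / 99.9% |
| 0.5 | 88.5% / 97.3% | 99.9% / 100% |
| 0.7 | 91.9% / 99.8% | 100% / 100% |

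The smallest N for more than 80% power with the signed-rank test is 10, 9, 7 and 6 for these four correlations.

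**Step 5: smaller effects.** These effect sizes are illustrative; neither is in the protocol. Both rows use 20 patients.
- Primary difference of 5 g: 61% / 84% at ρ = 0.5 and 64% / 96% at ρ = 0.7.
- Secondary outcome differing by 0.5 between-patient SD: about 27% / 54% at ρ = 0.5 and about 22–23% / 90–91% at ρ = 0.8.

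**Step 6: the interim boundary.** With 10 pairs the smallest exact two-sided signed-rank P is 2/2¹⁰ = 0.00195, above 0.001, so an efficacy stop could never occur. A rank-sum comparison of period differences between sequences, 5 against 5, has a minimum of 2/252 = 0.0079 and fails as well. The literal rank-sum test on 10 against 10 values can reach the boundary, and under the planned 10 g difference does so in about 21–24% of trials.

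**The case against.** **The rule on paired tests governs all tests, so a sensible analyst would use the paired Wilcoxon test.** Plausible, but not established. The power section used the unpaired test in earnest, as the reproduced figures show. As a planning device, ρ = 0 does no harm: the signed-rank test also needs N = 10 there, and positive correlation only helps.

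**The type I error is not breached.** This stands. The protocol promises a maximum of 0.05, and with positive correlation the rank-sum test stays below it. A reader might infer a false-positive risk or an invalid primary test; the documents do not support that.

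**The primary conclusion is hardly affected at the planned effect.** This also stands. The protocol treats about 10 g as the worst case for the optimized regimen, and its futility rule uses 9 g, where rank-sum power at 20 patients is at least 96.9%. The 5 g figures show direction only. There is still a moderate loss if exclusions, which the protocol expects to be many, leave about 10 analysable patients.

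**The weakness of null secondary results is disclosed.** Largely true. The analysis section says that confirmatory studies would be needed and plans a Monte Carlo analysis of the minimal detectable difference, and the Discussion says the trial cannot confirm equality. A reader might infer that the plan hides an insensitive test behind a claim of support; these caveats rule that out. They do, however, blame sample size alone. Part of the insensitivity would come from the test, and a sensitivity analysis using the same test would overstate the minimal detectable difference.

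**Conclusion.** The contradiction is real and concerns the test for the primary outcome, so it should be settled before the data are analysed. It is an error in what the document states, not detail left to a fuller plan.

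Its effect is loss of sensitivity, not invalidity. For assumed correlations of 0.3 to 0.7, the rank-sum test at 20 patients works at a true level of about 2% down to 0.1–0.2%. A reader might conclude that the sample size is inadequate. It is not: the stated power for 10 g reproduces, and it holds at 10 and 20 patients under either test. The practical cost falls on an analysis set near 10 patients (about 89% against 97% at correlation 0.5), on effects smaller than planned, and on the secondary outcomes.

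The choice of test also decides whether an efficacy stop is possible at 10 patients, so the analysis and interim sections have to be corrected together.

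These sizes rest on bivariate normal data with the protocol's SDs for the primary outcome, and on correlations and secondary effect sizes that the protocol does not give.

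**What to change.** 1. **Analysis of outcomes:** replace the rank-sum test with the Wilcoxon signed-rank test on within-patient differences (optimized minus standard), reported with the Hodges-Lehmann estimate and 95% confidence interval. Use the same paired test in the Monte Carlo sensitivity analysis for secondary outcomes.
2. **Sample size and power analysis:** rerun the simulation on paired differences over a stated range of correlations, for example 0 to 0.7, and restate the power. N = 10 and N = 20 should stand.
3. **Interim analysis:** either name an efficacy test that can reach P ≤ 0.001 with 10 pairs, such as a paired t test on the differences, or state that no efficacy stop is possible at 10 patients. State that the futility t test is paired.

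The cost is edits to three sections and one rerun of the simulation. Changing the test name alone would not be enough, because it would silently disable the efficacy stop. Data collection does not change.

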## Background

In peritoneal dialysis (PD), the peritoneum of the patient is used as a biological dialyzer membrane by filling and draining the peritoneal cavity with dialysis fluid at pre-determined time points. Excess water is removed from the patient by osmosis, which is usually induced by the presence of high concentrations of glucose in the dialysate. The patient absorbs a significant amount of this glucose. In the light of the growing number of diabetic patients on PD, this unwanted glucose absorption is problematic and often represents a clinical challenge. A recent meta-analysis indicated that around 50% of PD patients may develop a glucose disorder which can significantly increase mortality [1].

Automated peritoneal dialysis is PD performed with the aid of a machine, a cycler, which aids the patient or the caregiver from the tedious work of filling and draining the PD fluid. Novel cyclers allow the treatment to be varied in a multitude of ways and recently, it was shown, using a theoretical model, that automated peritoneal dialysis could be improved by using a modified “bi-modal” treatment regimen in which exchanges using no osmotic agent is alternated with short “UF exchanges” having an osmotic agent [2]. Especially, it was shown that the potentially harmful glucose absorption could be reduced by 20–30%. Thus, the potential benefits of the novel regimens appear to be substantial.

The current pilot study aims to evaluate the clinical safety and feasibility of such optimized regimens in a small study using the HomeChoice Pro cycler. Since HomeChoice does not support exchanges having different lengths, the treatment will be divided into a “UF-part” comprising all the UF cycles and a “Clearance part”. A nurse will supervise the treatment and switch between the two parts manually. Moreover, as 0% glucose PD fluid is not available, a 0.1% glucose hemodialysis (CRRT) fluid will be used. We will use 2.27% glucose (Dianeal) for the UF exchanges.

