## Method

### Hypothesis

We will test the hypothesis that there is a 10-g difference in terms of glucose absorption, between a standard APD (6 × 2 L 1.36% over 9 h) regime and an optimized APD regimen (7 × 2 L 2.27% + 5 × 2 L 0.1% over ~ 8 h) while there are no differences in osmotic water transport (“UF”), sodium removal, Kt/V creatinine, or Kt/V urea between the regimens.

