### Secondary outcomes

Secondary outcomes are osmotic water transport (“UF”), sodium removal, Kt/V urea, Kt/V creatinine, and incidence of complications up to 14 days post-intervention.

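### Complications fall under the same no-significant-difference condition as the transport outcomes, so an excess of 3 versus 0 in 20 patients would not block the supportive reading

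*Protocol article*

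**What the plan says.** All references are to the protocol article.

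- *Background* says that the pilot "aims to evaluate the clinical safety and feasibility of such optimized regimens in a small study".
- *Secondary outcomes* ends its list, after UF, sodium removal and Kt/V urea, with "Kt/V creatinine, and incidence of complications up to 14 days post-intervention".
- *Statistical analysis plan* restricts the analysis to patients who completed both regimens and states that "all hypothesis tests will be paired and two-sided, with a maximal type I error risk of 0.05".
- *Analysis of outcomes* opens with "Study outcomes will be analyzed using a Wilcoxon rank-sum test", without an exception. The rule that follows begins "In the event of no difference between the groups with regard to secondary outcomes and a difference in the primary outcome". With glucose absorption lower on the optimized regimen, such results are read as supporting the hypothesis. The same sentence asks for confirmatory studies because the small sample "may not be adequately powered to detect differences in the secondary outcomes". A Monte Carlo analysis of the minimal difference needed for significance in the secondary outcomes is then planned.
- The last paragraph of that section keeps the number of complications from being exploratory, but only when the primary outcome is negative or reversed.
- *Hypothesis* names glucose absorption and continues "while there are no differences in osmotic water transport (“UF”), sodium removal, Kt/V creatinine, or Kt/V urea between the regimens". Complications are not in it.

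**The concern.** The condition behind the supportive reading covers two kinds of outcome. For UF, sodium removal and Kt/V, the hypothesis predicts no difference, and the plan admits that 20 patients can show only large ones. Complications are different: they are a rare yes/no event, the question is how much harm can be excluded, and a non-significant test does not answer it. As written, complications count as not differing whenever P is 0.05 or more. No confidence limit or separate safety criterion applies to them in that branch.

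The other branches do not help. A significant difference in a secondary outcome that is not an improvement falls into the residual case, which compares the differences with those expected from the extended 3-pore model. That is a model of peritoneal transport and cannot interpret an excess of complications.

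At stake is how a pilot with a safety aim, run without a data monitoring board (*Good clinical practice and quality assurance*), will read a modest excess of complications when its primary result is favourable.

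**Working it through.** **Inputs.** From the document: 20 patients, each receiving both regimens; two-sided alpha 0.05; a rank-sum test in *Analysis of outcomes* but paired tests in *Statistical analysis plan*; an interim look after 10 completers. The document gives no complication rates, so the rates in step 5 are assumptions.

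**1. The plan's own power figure.** *Sample size and power analysis* reports more than 80% power at N = 10 and more than 98% at N = 20 for glucose absorption (44 g, SD 7.74, versus 34 g, SD 5.94). Simulating 10,000 exact rank-sum tests gives 0.769 at N = 9, 0.830 at N = 10 and 0.994 at N = 20. The figures reproduce, but they concern the primary outcome. No power is stated for complications.

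**2. Rank-sum test, k versus 0 of 20.** For 0/1 data the tie-corrected statistic without continuity correction satisfies z² = (39/40) × Pearson χ².
- k = 3: χ² = 40 × (3 × 20)² / (20 × 20 × 3 × 37) = 3.243; z² = 3.162; z = 1.778; p = 0.075. With continuity correction, p = 0.080.
- k = 4: χ² = 40 × (4 × 20)² / (20 × 20 × 4 × 36) = 4.444; z² = 4.333; z = 2.082; p = 0.037. With continuity correction, p = 0.040.

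**3. Exact versions.** The exact permutation form of the rank-sum test on 0/1 data is Fisher's test, with p = 2 × C(20,k)/C(40,k) for k versus 0. The exact paired test (McNemar) gives p = 2 × 0.5^k.

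| Split of 20 | Rank-sum, asymptotic | Fisher | Exact paired |
|---|---|---|---|
| 3 vs 0 | 0.080 | 0.231 | 0.25 |
| 4 vs 0 | 0.040 | 0.106 | 0.125 |
| 5 vs 0 | 0.020 | 0.047 | 0.0625 |
| 6 vs 0 | 0.009 | 0.020 | 0.031 |

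So 3 versus 0 is non-significant by all three tests. The largest excess over zero that passes is 3 by the asymptotic rank-sum test, 4 by Fisher's test and 5 by the exact paired test.

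**4. What the data could exclude.** The exact two-sided 95% upper limit for zero events is 1 − 0.025^(1/n): 16.8% for 0 of 20 and 30.8% for 0 of 10. For 3 of 20 the exact interval is 3.2% to 37.9%.

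**5. Power under assumed rates.** Standard versus optimized, sessions treated as independent, binomial or multinomial enumeration, asymptotic rank-sum with continuity correction.

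| Assumed rates | n | Rank-sum | Exact paired |
|---|---|---|---|
| 5% vs 15% | 20 | 0.15 | 0.03 |
| 5% vs 20% | 20 | 0.29 | 0.09 |
| 5% vs 25% | 20 | 0.44 | 0.20 |
| 5% vs 25% | 10 | 0.14 | 0.01 |

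**6. Who is counted.** *Post-allocation exclusion criteria* allows exclusion for in-trial peritonitis or catheter malfunction, and only completers of both regimens are analysed. Some patients with a complication may therefore never enter the comparison. Sessions may be 1 to 28 days apart (*Study interventions*) while complications are counted for 14 days. When the gap is shorter than 14 days the two windows overlap, and an event in the overlap cannot be assigned to one regimen by date alone.

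**The case against.** The strongest reply is that the plan already qualifies the result. The low-power caveat, the call for confirmatory studies and the minimal-difference analysis all refer to the secondary outcomes in general. If complications are a secondary outcome for the rule, they are one for the caveat too. This stands, and a reader who infers that nothing qualifies a non-significant complication result goes too far. What remains is that a minimal detectable difference describes the test and does not bound harm. The limitation in the *Discussion* also names only Kt/V, sodium removal and UF, and limits the follow-up analysis there to UF.

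A reader might also infer that a non-significant complications test by itself carries the trial to a favourable verdict, or clears the regimen as safe. The text supports neither. Lower glucose absorption and no difference in the other four secondary outcomes are also required, and the hypothesis being supported does not mention complications.

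It can further be argued that the condition was meant for transport outcomes only. The *Abstract* omits complications from its secondary endpoints, and the next branch speaks of clearance, sodium removal and UF. That is possible, but *Secondary outcomes* lists complications, and the section's closing paragraph counts them among the other outcomes. On the narrower reading, complications have no stated reading when the primary outcome succeeds, so the text needs the same correction.

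Finally, *Harms* provides for recording and reporting all adverse events. That serves surveillance during the trial; it does not settle how complications enter the trial's conclusion. Low power for rare events is indeed common to pilots of this size, which is the reason not to rest on a significance test here.

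**Conclusion.** The point holds in limited form. On the article's wording, complications sit under a rank-sum test and a no-difference condition together with UF, sodium removal and Kt/V. Provided that the other parts of the condition are met, an excess of up to 3 versus 0 of 20 (asymptotic rank-sum) or 5 versus 0 (exact paired) would not block the supportive reading. These thresholds assume 20 completers, all events counted, and each event assigned to one regimen. Which threshold applies depends on whether the paired or the unpaired test is used, since the two sections disagree. The power figures rest on assumed rates and independent sessions; the splits and confidence limits do not rest on assumed rates.

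The weakness lies in how a safety outcome is read in a pilot with a safety aim. It leaves the primary analysis untouched.

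**What to change.** In *Analysis of outcomes*, take incidence of complications out of the rank-sum test and out of the no-difference condition. In their place:

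- Report the number of patients with a complication after each regimen with exact 95% confidence intervals, for all patients who started a session and not only completers.
- List each event with its date relative to both sessions, so that events in overlapping 14-day windows are visible.
- State that non-significance will not be read as comparable safety, and give the upper limit that the data exclude (16.8% if no events occur in 20 patients).
- Add complications to the *Discussion* limitation on outcomes that the trial cannot resolve.

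The change is mainly wording. Adverse events are already to be recorded for all patients, so it needs no new measurements, only that non-completers are kept in the safety count. The downside is a less favourable-sounding safety statement.

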The main weakness in the current study is the small sample size, which means that there will be insufficient statistical power to detect anything but large differences in urea Kt/V, crea Kt/V, sodium removal, and UF. Hence, while theoretical modeling predicts no large difference in these parameters, this study cannot be used to confirm that finding. On the other hand, it may be argued that small differences in these parameters are more of a theoretical interest and, in practice, of little clinical interest. To further assess this notion, we will, in the case of non-significant outcomes in UF and small-solute transport, perform a sensitivity analysis to estimate the smallest detectable difference in UF between the treatment groups. Moreover, the theoretically expected difference in primary outcome is caused by two separate effects, namely, reduced glucose absorption due to a higher DFR, increasing the average dialysate glucose concentration, and also, the effect of a higher glucose concentration [3, 4] per se. The results in the current study cannot be used to distinguish between these two effects. Another weakness in the study is the simplicity of the power analysis where it was assumed that the sampling distribution is normal. However, since the actual nature of the sampling distribution is unknown, we chose the normal distribution since, according to the central limit theorem, the sampling distribution will tend to the normal distribution with increasing *N*. Lastly, choosing a non-parametric test may inflate the type II error rate [11] if the underlying distribution is truly normal, and there are no outliers. However, biological data typically does not satisfy one or more of these latter criteria and thus the use of parametric methods in medicine relies heavily on large sample sizes since the results of parametric tests are influenced to a higher degree than non-parametric tests both by outliers and deviations from a normal distribution.

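### Non-significant UF, sodium removal and Kt/V results are scored as support for a hypothesis of no difference, and a significant worsening has no stated verdict

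*Protocol article*

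**What the plan says.** All references are to the protocol article.

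- **Hypothesis:** the 10 g glucose difference is to hold "while there are no differences in osmotic water transport (“UF”), sodium removal, Kt/V creatinine, or Kt/V urea between the regimens". No margin is given for any of the four.
- **Analysis of outcomes** sets the verdicts:
  - "In the event of no difference between the groups with regard to secondary outcomes and a difference in the primary outcome" (lower absorption on the optimized regimen): "we will interpret such results as supporting our hypothesis but that confirmatory studies are needed using a higher number of patients". The reason given is that the low N "in the current study may not be adequately powered to detect differences in the secondary outcomes". A Monte Carlo step will then "quantify the minimal difference needed to yield a significant difference in the secondary outcomes".
  - Primary positive and secondaries significantly different: supportive if the difference is an improvement.
  - Otherwise: "In any other case, the differences will be compared to the differences expected theoretically according to the extended 3-pore model".
  - Primary negative or reversed: all other outcomes except complications become exploratory.
- **Discussion:** power is adequate only for large differences in UF, sodium removal and Kt/V. On the model's prediction of no large difference, "this study cannot be used to confirm that finding".

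**The concern.** Less glucose absorbed is of use only if fluid and solute removal are kept, so the second half of the hypothesis carries the clinical meaning of the first. That half is judged by a non-significant test of difference. Such a result arises when the regimens are equivalent, and also when the trial is too small to see a real loss. The rule does not separate the two and gives both the same label.

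The rule is also incomplete on the unfavourable side. With a positive primary, no difference and improvement each have a verdict. A significant fall in UF or clearance has none, although it is the result that would most directly refute the hypothesis as written. At stake is the headline conclusion: a report could say that the hypothesis is supported while the data remain compatible with a meaningful loss of UF or clearance.

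**Working it through.** **1. What no difference means.** The next paragraph of Analysis of outcomes contrasts it with a significant difference, and the Discussion speaks of non-significant outcomes. It therefore means P ≥ 0.05.

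**2. The article's own power figure.** Inputs (Sample size and power analysis): Normal(44, SD 7.74) against Normal(34, SD 5.94), two-sided rank-sum test, P < 0.05. Simulated power is about 76–77% at N = 9, 83% at N = 10 and 99% at N = 20. This agrees with the stated first crossing of 80% at N = 10 and > 98% at N = 20. It concerns glucose absorption only.

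**3. Test used below.** The section Statistical analysis plan says that all tests are paired; Analysis of outcomes names the rank-sum test, which is unpaired. That is a separate matter. I use the exact paired signed-rank test, which is the reading more favourable to the plan.

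**4. Chance of missing a real loss in one secondary.** The article gives no SD for these outcomes, so the loss is expressed in units of the SD of the within-patient difference (simulation, 60,000 runs).

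| | N = 10 | N = 20 |
|---|---|---|
| Power, true loss 0.5 SD | 28% | 54% |
| Non-significant (1 − power) | 72% | 46% |
| Loss detected with 80% power | about 1.0 SD | about 0.68 SD |

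N = 10 stands for a trial that ends with 10 usable patients. The article analyses completers only and expects many exclusions after allocation.

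**5. Requiring a significant primary.** With the article's glucose inputs and outcomes taken as independent, SD of the difference = √(7.74² + 5.94²) = 9.76 g, so 10 g is 10/9.76 = 1.02 SD. Signed-rank power is about 80% (N = 10) and 99% (N = 20).

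P(support) = P(primary significant) × P(secondary non-significant)

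- N = 10: 0.80 × 0.72 = 0.58
- N = 20: 0.99 × 0.46 = 0.45 (0.453 before rounding)

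These treat one secondary alone. If the other three are truly unchanged, independent, and must also be non-significant, each figure is multiplied by about 0.95³ = 0.86.

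**6. Percentage scale.** Assume a CV of 18% (range 10 to 30%), borrowed from the article's figures for glucose absorption, and a within-patient correlation of 0.5. Then SD of the difference = CV × √(2 × (1 − 0.5)) = CV. A true 10% loss is non-significant in 66% of trials at N = 10 (range 21 to 84%) and 38% at N = 20 (range 2 to 73%).

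**7. What the Monte Carlo step adds.** The minimal difference that would reach significance describes the resolution of the test. It does not use the observed difference to show which losses are excluded, and it is compared with no acceptable loss. A 95% CI does the former. Under the assumptions of step 6 its half-width is t × CV/√N:

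- N = 10: 2.262 × 18/√10 = 12.9% of the mean (range 7.2 to 21.5%)
- N = 20: 2.093 × 18/√20 = 8.4% of the mean (range 4.7 to 14.0%)

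**The case against.** The best defence is that the article is candid. It calls itself a pilot, attaches a need for confirmation to the supportive verdict, gives low power as the reason, repeats the limitation in the Discussion and plans a detectable-difference analysis. This stands, and it lowers the severity. It does not change the verdict word: a result that cannot tell no loss from an unseen loss is still filed as support.

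It is also fair that interval reporting for secondary outcomes is often left to a statistical analysis plan. The point here is narrower: the article itself fixes the decision rule.

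Three stronger readings are tempting but not supported.

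- A reader might infer that Analysis of outcomes and the Discussion flatly contradict each other. They do not: support that needs confirmation and an inability to confirm can be held together, and both rest on low N. There is tension over the word support.
- A reader might infer that no secondary result can count against the hypothesis. Significant differences are supportive only if they are improvements, so a worsening fails that condition, and it conflicts with the Hypothesis section on its face. What is missing is the stated verdict.
- A reader might infer that a smaller or noisier trial always makes support easier. The primary must also be significant. In the setting of step 5, support is declared in about 45% of trials at N = 20, 58% at N = 10, 48% at N = 7, 33% at N = 6 and 0% at N = 5. Raising the glucose CV from 18% to 30% cuts primary power at N = 10 from about 80% to 38%.

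**Conclusion.** The point holds in a limited form. Non-significance on UF, sodium removal and Kt/V is treated, with a positive primary, as support for a hypothesis that includes no difference on them, and a significant worsening has no stated negative verdict. Under the illustration, support would be declared in about 45% (N = 20) to 58% (N = 10) of trials despite a real 0.5 SD loss in one secondary.

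Those figures rest on a paired test, independent outcomes, the article's glucose inputs and an effect size chosen for illustration. Nothing in the article says whether 0.5 SD is a clinically relevant loss. The fault in the rule does not depend on them. Given the pilot status and the disclosed caveats, this should be fixed, but it does not invalidate the trial.

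**What to change.** Amend Analysis of outcomes before the data are analysed:

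1. Limit the claim supported by a positive primary to glucose absorption.
2. Report the within-patient difference with its 95% CI for UF, sodium removal, Kt/V urea and Kt/V creatinine, in place of or alongside the Monte Carlo step.
3. Have the investigators state, before analysis, the largest acceptable loss for each. Call a non-significant secondary inconclusive unless its CI excludes that loss.
4. State that a significant worsening in any of the four means that the no-difference part of the hypothesis is not supported. The comparison with the 3-pore model can stay as explanation.

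The cost is a few sentences and agreement on four margins, with no new data or patients. The downside is that some secondaries will probably be reported as inconclusive, which is close to what the Discussion already concedes.
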